**Methods/design:**

PLEASANT is a cluster randomised trial. A total of 140 General Practices (GPs) will be recruited into the trial; 70 GPs randomised to the intervention and 70 control practices of “usual care”. An average practice is expected to have approximately 100 children (aged 4–16 with a diagnosis of asthma) hence observational data will be collected on around 14000 children over a 24-month period. The Clinical Practice Research Datalink will collect all data required for the study which includes diagnostic, prescription and referral data.

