**Figure 1 F1:**
[figure not shown]
**Mean residuals for excess medical contacts for children with asthma for over controls in England.** The vertical lines represent, from left to right, the 1st September, 1st January and 1st April with LOESS smoothing curve that enables trends to be seen [13].

It could therefore be argued that July and August are a good time to have asthma; the pollen season is almost over, school age children are not at school and so have less opportunity to pick up any viral infections that are going through the population.

In the same study we also observed a drop in prescriptions for inhaled steroids in August immediately preceding the return back to school with 25% fewer prescriptions in August compared to July and September [13] (see Figure 2). This drop in prescriptions precedes the viral challenge of a return back to school. We further showed that patients who received a prescription for inhaled corticosteroid had 0.14 fewer contacts per patient (95% CI 0.12 to 0.16, P < 0.001, England; 95% CI 0.10 to 0.18, P < 0.001, Scotland) than those who did not receive an August prescription.

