### Data collection

#### Clinical Practice Research Datalink

The CPRD is a computerised database of anonymised longitudinal medical records from primary care [18]. The CPRD are able to capture all medical contacts, from prescription request through to out of hours contacts, along with the reason for the contact. This therefore negates the need to request this information from the GP, reduces practice burden, and ensures complete data sets.

CPRD will extract data from GP medical records 3 times; baseline (NHS contacts for the previous 12 months) and at 1 month and 12 months post intervention. The study team will not have access to any patient identifiable data and will receive all data fully anonymised.

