### Statistics

#### Sample size

From previous research in the CPRD practice population 30% of school age asthmatic children had at least one unscheduled medical contact within the month of September [13]. We postulate that the intervention may reduce the number of children who have unscheduled medical contacts from 30% to 25% (i.e. an absolute reduction of 5%). This gives an effect size of 5%. The average practice size in the CPRD is 8,294. We thus anticipate circa 100 school-age asthmatic patients per practice (based on 12% of a practice being school age children and 11% of school-age children having asthma). Hence, to detect a difference of 5% with 90% power and two-sided significance level of 5%, with an intra-class correlation (ICC) of 0.03 to account for clustering we require 70 practices per arm. The sample size of 140 practices would equate to approximately 14,000 school age asthmatic patients.

Ukoumunne et al. [19] give estimates of ICCs for patients with respiratory symptoms in symptoms in General Practice. Based on the work of Ukoumunne et al. an ICC of 0.03 is a conservative estimate. The power of the study for ICCs of 0.01, 0.02, 0.03, 0.04 and 0.05 is respectively 99.4, 96.0, 90.0, 83.1 and 76.2%.

As a further sensitivity analysis we will investigate the effect of practices not sending out the letter as planned. Suppose 10 practices failed to send out the letter, these would still be included in the primary analysis under the intent-to-treat principle. However, the effect that could be observed would be reduced to 4.3%. Under the sample assumptions (ICC = 0.03, etc.) the power for the same sample size is reduced to 79.3%. This is a little under 80% but it does demonstrate that the study is reasonably robust to at least one deviation in the planned design.

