#### Data analysis

The study periods are defined in three stages. The primary study period is 1st – 30th September 2013, since this is the period when the intervention is felt likely to impact. The extended study period is 1st September - 31st December 2013, since asthma-related appointments are more frequent in the entire period. The follow-up period is 12 calendar months from 1st September 2013 to 31st August 2014.

The primary analyses will be by intent-to-treat among patients aged 5–16 years as of 1st September 2012. The primary endpoint (the proportion of patients who have an unscheduled medical contact in September) will be analysed by logistic regression in which the covariates will include the individual's age; gender; number of contacts the previous September; the trial arm (intervention or control); and the design/cluster effect of general practice as a random effect.

The same approach will be used for analyses based on the extended period. The proportion of patients who have an unscheduled medical contact, the proportion of patients who have any medical contact; and the proportion of patients who have an unscheduled medical contact associated with respiratory illness. The number of unscheduled medical appointments per patient in the extended period; the total number of medical contacts (scheduled and unscheduled) per patient in the extended period; the number of unscheduled medical contacts per patient associated with a respiratory diagnosis in the extended period; the number of prescriptions per patient in the month of August; and the number of prescriptions per patient in the 12 months following the intervention will be analysed in an analogous approach to the primary endpoint. A random effects negative binomial model will be fitted, including the same covariates as above. Further analyses will address the time to first medical contact (defined as the number of days from the start of school term (2nd September 2013) to the date of first appointment, up to and including December 2013, the time to first medical contact up to and including December 2013, and the time to first unscheduled medical contact associated with a respiratory diagnosis. These analyses will be conducted using a random effects ("shared frailty") regression model including the same covariates as described previously.

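### The models for August and 12-month prescriptions adjust for contacts in the previous September instead of each patient's own earlier prescription count

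*Protocol article*

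**What the plan says.** In the protocol article (Methods/Design, Statistics, Data analysis), the primary logistic model adjusts for age, gender, the count of contacts in the previous September and trial arm, with practice as a random effect. The same section then lists the count outcomes, among them "the number of prescriptions per patient in the month of August" and the corresponding count for the 12 months after the intervention. For all of them it says: "A random effects negative binomial model will be fitted, including the same covariates as above". No earlier prescription count is named for any model.

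Three other places bear on whether such a baseline exists:

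- The abstract describes data over 24 months, "which includes diagnostic, prescription and referral data".
- Data collection describes the first extract as "baseline (NHS contacts for the previous 12 months", from a database whose contacts include prescription requests. No start date is given.
- The inclusion criteria require asthma medication to have been prescribed in the previous 12 months.

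The Background gives the reason for an August outcome: "we also observed a drop in prescriptions for inhaled steroids in August".

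**The concern.** The trial's reasoning runs from the letter, to prescriptions collected in August, to fewer unscheduled contacts in September. The prescription counts are the outcomes nearest the start of that chain. If the primary result is null, they help to separate a letter that changed nothing from one that changed prescribing without changing contacts.

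A history covariate earns its place by predicting the outcome. A child's contacts in one past September should say less about prescribing in August, or over a year, than the same child's earlier prescriptions would. Randomisation is stratified by practice size only, so prescribing habits may differ between arms by chance, and the named covariate is poorly placed to adjust for that. At stake is the sharpness of these two comparisons.

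**Working it through.** **The plan's own figure.** The only stated power is for the primary endpoint. Inputs from the Sample size section: 30% against 25%, two-sided 5%, about 100 patients per practice, and "with an intra-class correlation (ICC) of 0.03 to account for clustering we require 70 practices per arm".

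- Design effect: 1 + 99 × 0.03 = 3.97.
- Effective number per arm: 70 × 100 / 3.97 = 1,763.
- Power: 91.4%, against 90.0% stated.

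That is close enough to count as reproduced. It uses no covariate adjustment, and the plan states no power for a prescription outcome.

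**How well the covariate fits each outcome.**

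| Outcome | Fit of previous-September contacts |
|---|---|
| Contacts in September | Close |
| Contacts, September to December | Partial |
| Prescriptions in August | Different variable, different month |
| Prescriptions over 12 months | Different variable, one month against twelve |
| Scheduled contacts, August and 12 months | No model named in Data analysis |

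The clear mismatch is confined to the two prescription counts.

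**Size if one correlation applies at both levels.** The documents give no correlations, so these are assumptions: 0 to 0.3 between the outcome and previous-September contacts (r_S), and 0.3 to 0.7 between the outcome and its own earlier count (r_M). On a linear approximation, substituting one covariate for the other multiplies the variance of the treatment effect by (1 − r_M²) / (1 − r_S²).

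| r_S | r_M | Variance ratio | SE ratio | A test with 80% power would have |
|---|---|---|---|---|
| 0.3 | 0.3 | 1.00 | 1.00 | 80% |
| 0.2 | 0.5 | 0.75 / 0.96 = 0.78 | 0.88 | 88.7% |
| 0 | 0.7 | 0.51 / 1.00 = 0.51 | 0.71 | 97.5% |

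**Size when the two levels differ.** Borrow the primary endpoint's ICC of 0.03, since none is given for prescriptions, with 100 patients per practice. Without a useful history covariate, the variance is proportional to 0.03 + 0.97/100 = 0.0397. With one, it is 0.03 × (1 − r_B²) + 0.0097 × (1 − r_W²), where r_B is the between-practice and r_W the within-practice correlation. For r_W = 0.5:

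| r_B | Variance ratio |
|---|---|
| 0 | 0.0373 / 0.0397 = 0.94 |
| 0.5 | 0.75 |
| 0.7 | 0.0226 / 0.0397 = 0.57 |
| 0.9 | 0.33 |

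Only 0.0097 / 0.0397 = 24% of the variance lies within practices, so the between-practice correlation largely decides the gain.

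**Whether the data reach back far enough.** The letter goes out in the week of 29 July 2013. A 12-month extract ending just before it would cover August 2012. One ending on 31 August 2013 would start on 1 September 2012 and miss it. Both would cover September to December 2012.

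**The case against.** The strongest reply is that this is detail for the SAP. The covariate list is introduced as what the models will include, so it is not closed, and a fuller description is deferred to an SAP to be finalised before post-intervention data arrive. That stands in part: the SAP can still add a better baseline. But the article has already chosen a history covariate for the prescription counts, so this is a stated choice that fits those outcomes poorly.

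Several stronger readings are tempting, and the documents do not support them:

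- *Every secondary model is mismatched.* For September contacts the covariate is close to the right baseline, and for September to December it is a partial match.
- *The trial discards a baseline it already holds.* The baseline extract is worded as contacts and has no start date, and the Study design section speaks of 12 months of data where the abstract has 24. Availability is likely, but it is an inference.
- *August prescribing is the only direct check on behaviour.* Scheduled contact in August is also a secondary outcome, and the letter invites contact with the practice.
- *The outcome counts all drugs and should be restricted to inhaled steroids.* The article leaves the type of prescription undefined. The letter and the inclusion criteria concern asthma medication generally, so restricting the outcome would be a preference.
- *A matched baseline is worth 18 to 50% more practices.* That follows from assumed correlations of 0.4 to 0.6 against 0.1 to 0.2 (0.99/0.84 = 1.18; 0.96/0.64 = 1.50), but it ignores clustering. If the baseline explained only within-practice variation, r = 0.4 to 0.6 would save 0.16 × 24% to 0.36 × 24%, about 4 to 9% of the variance.

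**Conclusion.** The point holds for the two prescription models and is minor. As written, they adjust for a contact count from the previous September when an earlier prescription count is the natural baseline and is probably obtainable. The loss is precision and adjustment for chance imbalance in prescribing.

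The documents do not determine its size. The range of about 1.00 to 0.51 in the variance ratio rests on assumed correlations, an ICC borrowed from the primary endpoint where clustering is shown, and a linear approximation to a random-effects negative binomial model. These are not bounds: a weak between-practice correlation leaves little gain, and one above 0.7 would give more.

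A reader might infer that the prescription comparisons are biased or that the main result is weakened. Neither follows. Allocation is random, the practice random effect carries between-practice variation into the standard error, and the primary endpoint, sample size and stated power do not depend on these models.

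**What to change.** In the SAP, before post-intervention data are received:

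1. In the August prescription model, add each patient's prescription count for August 2012, or use it in place of previous-September contacts. Adding is the safer choice, because it loses nothing material if the September count also predicts.
2. In the 12-month prescription model, do the same with the prescription count for the 12 months before the letter. That window should close before the week of 29 July 2013, so that the covariate cannot be affected by the intervention.
3. Count prescriptions in the same way for the baseline and the outcome.
4. First confirm that the baseline CPRD extract includes prescriptions and reaches 1 August 2012; if it does not, move its start date.

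As an optional refinement, use September to December 2012 values for the extended-period outcomes if the extract covers them. The cost is SAP wording and possibly a slightly earlier extract start. Practices supply nothing further, and the primary analysis does not change.

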#### Economic evaluation

An exploratory economic evaluation will be undertaken to compare the incremental cost per quality adjusted life year (QALY) of the intervention versus standard care. The perspective of the analysis will be that of the NHS and Personal Social Services. The time horizon will be one year from the intervention and therefore no discounting will be applied.

Data on the number and type of medical contacts in the intervention and control arms will be collected through the CPRD, and combined with PSSRU unit costs [14] and Department of Health reference costs [15] to assess the cost of medical contacts in each arm. Unscheduled contacts in September will be included to capture the impact of any reduction in asthma exacerbations. Scheduled contacts in the year following intervention will be included to capture any change in health care resource use in response to the letter. These will be reported separately in addition to reporting the overall costs of medical contacts for each arm. Prescription costs will be assessed for the year following intervention by combining data on the number of prescriptions with unit cost data from the British National Formulary (BNF). The costs for prescriptions and medical contacts will be combined to give overall costs in the control arm. In the intervention arm the overall cost will also include the cost of sending out the intervention, which will be based on the national primary care costing template from the UK National Institute for Health Research (NIHR) Primary Care Research Network (PCRN) [21].

An existing systematic review [22] has found evidence showing that asthma exacerbations have a significant impact on quality of life [23]. This review will be updated to identify any more recent publications, and literature evidence will be used to determine the health-related quality of life decrement associated with an asthma exacerbation that results in an unscheduled medical contact. From this the QALY gain of preventing asthma exacerbations with be estimated. We will assume that the intervention has no effect on survival and therefore any QALY gain will be wholly driven by improvements in quality of life achieved by preventing asthma exacerbations.

This evidence will inform a simple decision-analytic model to estimate the mean costs and QALYs for the intervention and control groups. Univariate sensitivity analyses and probabilistic sensitivity analyses will be used to examine the uncertainty in the model, with results displayed using cost-effectiveness planes and cost-effectiveness acceptability curves [24].

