### Trial intervention

A brief postal intervention (letter) has been designed specifically for the PLEASANT trial, developed with input from the study team, which includes a GP, Psychologist and Consultant Respiratory Paediatrician as well as the trial steering committee. It has also been discussed in detail, and reviewed, at two patient and public events that included school aged children with asthma and their parents.

The letter highlights the potential risks associated with stopping, or running low on, asthma medication during the school summer holidays and the effect this may have on exacerbation of asthma when returning to school. It encourages maintaining, or restarting if stopped, medication and to contact the GP or practice nurse if a prescription is required or clarification is needed on the dose. A copy of the intervention/letter is available upon request and will be published on the PLEASANT website from October 2013.

The intervention will be sent, from the GP, to the parents/carers of children with asthma at the beginning of the summer school holidays (week commencing 29th July 2013).

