### Allocation of scheduled versus unscheduled contacts

Every NHS service contact is coded by the GP practice and captured within the practice database. Using these codes we will allocate to either scheduled or unscheduled contact.

A scheduled contact is defined as any contact that is part of the planned care for the patient, for example an asthma review; a medical review; repeat prescription or immunisation. An unscheduled contact will be any contact not part of the patient’s care plan that is either patient initiated or as a result of illness.

To ensure the allocation of scheduled and unscheduled contacts are robust an adjudication panel, consisting of 3 GPs, will independently review the prescription and diagnosis codes allocating to either scheduled or unscheduled contact.

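### The economic evaluation costs unscheduled contacts in September only, inside a one-year horizon that applies in full to scheduled contacts and prescriptions, so the incremental cost can be wrong in either direction

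*Protocol article*

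**What the plan says.** The Economic evaluation section of the protocol article states: "The time horizon will be one year from the intervention and therefore no discounting will be applied". It then gives a window for each cost component.

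- Unscheduled contacts: "Unscheduled contacts in September will be included to capture the impact of any reduction in asthma exacerbations".
- Scheduled contacts: "Scheduled contacts in the year following intervention will be included to capture any change in health care resource use in response to the letter".
- Prescriptions: "Prescription costs will be assessed for the year following intervention".

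The overall cost in each arm is built from these components, plus the cost of the mailing in the intervention arm. The QALY gain comes entirely from prevented exacerbations, valued through the "health-related quality of life decrement associated with an asthma exacerbation that results in an unscheduled medical contact". Univariate and probabilistic sensitivity analyses are planned, but none is named for the time window.

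Two other sections bear on the point. Under Trial intervention, the letter goes out in the week of 29 July 2013 and encourages families "to contact the GP or practice nurse if a prescription is required or clarification is needed on the dose". Under Allocation of scheduled versus unscheduled contacts, a contact outside the child's care plan "that is either patient initiated or as a result of illness" is unscheduled, while reviews and repeat prescriptions are scheduled.

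**The concern.** The unscheduled component covers 1 of the 12 months in the horizon; the other contact and prescription components cover all 12. September is also the month chosen because the effect is expected there. An unscheduled contact that leaves September for any other month of the year drops out of the tally and is not picked up again. An unscheduled contact that the letter prevents in October or later is not credited, while any extra year-round prescribing and reviews are charged.

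August is the least visible month. It falls inside the year from the mailing and is when the letter would first prompt contacts. Any of these that are classed as unscheduled enter neither the costs nor a listed outcome: the August outcomes are prescriptions and scheduled contacts.

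At stake is the incremental cost per QALY, which the Discussion says will gauge any saving from a letter that might be adopted in routine care.

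**Working it through.** The article reports no economic result, so there is no figure to reproduce. The check sets the windows side by side and then traces what each costing rule would book.

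**Windows for unscheduled contacts**

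| Period | In the costs? | In a listed outcome? |
|---|---|---|
| August 2013 | No | No |
| September 2013 | Yes | Yes (primary and secondary) |
| October–December 2013 | No | Yes, within the September–December outcomes |
| January 2014 to end of horizon | No | No |

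**Inputs**

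- Unit cost of a surgery contact: £36 (Background). This is the lowest unit cost listed there.
- September effect: 30% to 25% of children (Sample size). Assumption: read as 5 fewer contacts per 100 children. The protocol states it as a proportion of children with at least one contact.
- Children per arm: 70 practices × 100 = 7,000.
- d = unscheduled contacts per 100 children that reappear or are newly prompted outside September; b = further contacts per 100 prevented outside September. The documents give neither, so a range is shown.

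**Formulas, per 100 children**

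- September-only saving = 5 × £36 = £180, whatever d and b are.
- 12-month saving = (5 − d + b) × £36.
- Error of the September-only rule = (d − b) × £36. It overstates the saving when d exceeds b and understates it when b exceeds d.

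**Results**

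| Assumption | September-only, per 100 | 12-month, per 100 | 12-month, per 7,000 (× 70) |
|---|---|---|---|
| No displacement (d = 0, b = 0) | £180 | 5 × £36 = £180 | £12,600 |
| 25% displaced (d = 1.25) | £180 | 3.75 × £36 = £135 | £9,450 |
| 50% displaced (d = 2.5) | £180 | 2.5 × £36 = £90 | £6,300 |
| 75% displaced (d = 3.75) | £180 | 1.25 × £36 = £45 | £3,150 |
| 100% displaced (d = 5) | £180 | £0 | £0 |
| 2 more prevented elsewhere (b = 2) | £180 | 7 × £36 = £252 | £17,640 |
| 5 more prevented elsewhere (b = 5) | £180 | 10 × £36 = £360 | £25,200 |

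The September-only column never moves. That is the defect: the rule cannot tell these situations apart.

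**The case against.** Several arguments stand on the other side.

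- **The restriction is not spelled out.** The text never says that unscheduled contacts from other months are excluded. But one month beside two year-long windows has no other plain reading, and no section adds the other months. These windows are stated choices, not details that a condensed article leaves to a fuller document.
- **A September focus fits the hypothesis.** The Data analysis section names September as the month when an effect is most likely, and wider windows add noise. This supports showing September separately. It does not support leaving out the rest of a horizon the plan itself sets, particularly as the same section defines an extended period to December because asthma-related appointments are more frequent throughout it.
- **Much letter-prompted demand is costed.** Reviews and repeat prescriptions count as scheduled and are costed for the year. This stands: the gap covers only prompted contacts that the adjudication panel classes as unscheduled.

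A reader might infer that the plan is tilted in favour of the letter. The documents do not support that: year-long scheduled and prescription costs are charged while later prevented contacts earn nothing, so the rule can also work against the letter. A reader might also infer that displacement would be hidden throughout the trial. Delay into October–December would show in the September–December secondary outcomes; it is missing only from the economic tally. The Safety section also says unscheduled and emergency contacts for asthma complications will be described in the final report, though it does not feed them into the costs. Finally, a reader might suppose that the quality-of-life decrement is to be applied to contacts for any cause. The text ties it to an asthma exacerbation leading to an unscheduled contact, so there is nothing to correct there.

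**Conclusion.** The concern holds as a mismatch between the stated horizon and the window for one cost component, with possible bias of unknown sign. On the assumptions shown, the September-only figure of £180 per 100 children would stand against a 12-month figure anywhere from £0 to £360. The full £12,600 per 7,000 children would be spurious only under complete displacement, which is one end of an assumed range and not an estimate. Nothing in the documents shows that displacement, prompted unscheduled demand or later benefit will occur, or that amounts of this size would change a conclusion.

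The same fault reaches the QALY gain if prevented exacerbations are counted in September only. The sentence on September contacts suggests this, but the section does not state it. The weight is moderate: the evaluation is labelled exploratory, its contact components will be reported separately, and the primary endpoint and its inference are untouched. The change is still worth making.

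**What to change.** In the base case, cost unscheduled contacts, and derive prevented exacerbations for the QALY gain, over the same 12 months from the intervention as scheduled contacts and prescriptions. State that the window starts at the mailing: the follow-up period in the Data analysis section starts on 1 September and would leave August 2013 out. Present September and September–December as separate components or sensitivity windows. Report unscheduled contacts in August by arm, so that any demand prompted by the letter can be seen.

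The cost is a little more analysis and a noisier cost difference, because months with little expected effect are added. No new data collection should be needed: the planned CPRD extraction runs to 12 months after the intervention, and August data are already required for two secondary outcomes.
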